##### Interim analysis

Given that CRT is known to be effective, we want to ensure that we do not adopt all four trial arms if one treatment arm provides little benefit compared with the remainder, so we will carry out an interim intention-to-treat analysis. This will be undertaken by the health economist, using data from the first 195 patients (using the post-therapy data at 15 weeks post-randomisation). This analysis may result in one of the trial arms being closed, with an immediate impact on the randomisation of the next patients.

The decision to drop an arm will be taken by an independent data monitoring committee and will depend on the resultant cost of therapy and other services and goal attainment. The costs will include direct therapy inputs and other services derived from the Client Service Receipt Inventory.

The direct therapy costs will be calculated from data on the number and length of sessions, number of attendees (for group therapy) and unit costs, based on staff grade and overheads. Cost-effectiveness planes will be generated by plotting the 1000 incremental cost–outcome combinations for each pair of comparators. This will tell us the probability that one therapy has (i) lower costs and better outcomes, (ii) lower costs and worse outcomes, (iii) higher costs and better outcomes, or (iv) higher costs and better outcomes than a comparator.

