### Allocation and blinding

Therapists use secure email to send a list of (11–15) consenting and assessed participants to the King’s Clinical Trials Unit, which allocates each participant using pre-generated randomisation lists. The randomised allocations are sent back to the therapist by secure email. The pre-generated randomisation lists are stored by the King’s Clinical Trials Unit in an access-restricted electronic folder that is not accessible to any members of the study team. The therapist informs each of the participants of their allocated trial arm.

Randomisation is stratified by research site in the proportion 4:4:3:4 (Group CRT, independent CRT, intensive CRT, treatment as usual) to make efficient use of therapist resources. Alternative randomisation allocations will be used if 15 participants cannot be recruited within the stipulated 12-week recruitment period, with a minimum block of 11 participants (reducing the proportions in the independent CRT and treatment-as-usual arms only so as not to break the group design constraint or reduce the number of participants in the intensive CRT arm). This flexibility allows more efficient use of therapist time and resources as the therapist time is limited and the intensive therapy absorbs a lot of this resource.

The whole team, apart from the therapists and the randomisation statistician, are blind to participant group allocation. Breaches will be recorded; if a breach is to a research assessor, another research worker will complete the assessment. An audit of the quality of the blinding will be conducted at the end of the study.

Participant data are entered online into a secure electronic data capture system hosted by the King’s Clinical Trials Unit separately from treatment allocation data. Data quality and audit are regularly tested prior to and after data entry. Analysis scripts are agreed and finalised by the senior statistician prior to unblinding.

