### Governance and monitoring

The trial is sponsored by King’s College London, overseen by a National Institute for Health Research (NIHR) appointed ECLIPSE program steering committee, to which the trial’s independent data monitoring committee report. All members of the data monitoring committee are independent of the trial (are not involved with the trial in any other way and do not have competing interests that could impact the trial). The membership of all the committees can be found in Additional file 2: Table S2. The data monitoring committee is the only body involved in the trial that has access to the unblinded comparative data. It will receive and review the progress and accruing data of the trial and provide advice on the conduct of the trial to the trial steering committee. The role of its members is to monitor these data and make recommendations to the program steering committee on whether there are any ethical or safety reasons why the trial should not continue. Further details can be found in the data monitoring committee charter, which is based on DAMOCLES study group guidance [65]. Adverse events are reviewed by local principle investigators and stored locally. Serious adverse events are reported (emailed) within one working day to the local principle investigator and trial co-ordinator using password-protected forms. All serious adverse events are reviewed by a chief investigator to make a decision on whether or not they are definitely, possibly, or not related to the study intervention and whether they are expected or unexpected. All serious adverse events are anonymised and sent to a designated member of the data monitoring committee for their decision on whether they must be reported to the research ethical committee.

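### The interim comparison by arm is given to a health economist whom the protocol counts as blind, and the arm-closure wording does not exempt treatment as usual, the comparator in every primary contrast

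*Protocol article*

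**What the plan says.** All references are to the protocol article.

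- **Who runs the interim (Interim analysis):** "This will be undertaken by the health economist, using data from the first 195 patients". The data are the 15-week outcomes.
- **What the analyst handles (Interim analysis):** "The direct therapy costs will be calculated from data on the number and length of sessions, number of attendees (for group therapy) and unit costs".
- **Who is blind (Allocation and blinding):** "The whole team, apart from the therapists and the randomisation statistician, are blind to participant group allocation". The same section has analysis scripts finalised before unblinding.
- **Who sees comparative data (Governance and monitoring):** "The data monitoring committee is the only body involved in the trial that has access to the unblinded comparative data".
- **What may be closed (Interim analysis):** the aim is that "we do not adopt all four trial arms if one treatment arm provides little benefit compared with the remainder". The consequence is put as "This analysis may result in one of the trial arms being closed, with an immediate impact on the randomisation of the next patients".
- **Who closes it (Interim analysis):** "The decision to drop an arm will be taken by an independent data monitoring committee", on cost and goal attainment. Governance and monitoring describes the committee as advising and making recommendations to the steering committee.
- **What depends on TAU (Analysis):** each primary comparison sets one CRT arm against TAU. Interventions adds that TAU is included so that cost-effectiveness can be assessed.

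**The concern.** Two things are at stake.

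The first is the blind in the analysis team. The health economist would see goal attainment and cost by arm while recruitment continues and before the final scripts are fixed. If the same person then works on the final economic evaluation, choices of unit cost, regression model and sensitivity analysis could be made with knowledge of the direction of the results.

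The second is the comparator. The set of arms is described as four, which includes TAU, and nothing says that TAU must stay open. Closing a CRT arm costs one contrast and strengthens the others. Closing TAU weakens all three primary contrasts at once and leaves later CRT patients without concurrent controls. Closure acts on randomisation immediately, so the wording has to be settled before the interim.

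**Working it through.** **Blinding: the passages side by side.**

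1. The interim compares arms on outcome and cost, so the analyst needs data by arm.
2. Dummy arm codes would not hide the arms. TAU has no CRT sessions, group CRT is the arm with attendee numbers, and intensive and independent CRT differ in therapist contact (Interventions).
3. The health economist is neither a therapist nor the randomisation statistician, so falls under the blind team in Allocation and blinding.
4. Nothing places the health economist on the data monitoring committee, whose members have no other role in the trial (Governance and monitoring).

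The task in Interim analysis therefore conflicts with the exception list in Allocation and blinding and, read strictly, with Governance and monitoring.

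**Closing TAU: inputs.** Total 720 (Abstract), ratio 4:4:3:4 for group, independent, intensive and TAU (Allocation and blinding), effect 0.3 SD and baseline correlation r = 0.5 (Power). Two-sided 5% is assumed, because the level is not stated.

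**Formula.** Power = Φ(0.3 / (s·√(1/n₁ + 1/n₂)) − 1.96), with s = 1 unadjusted and s = √(1 − 0.5²) = 0.866 for r = 0.5.

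**The plan's own figures.** 900 × 0.8 / 4 = 180 per arm. Unadjusted power is Φ(2.846 − 1.96) = 81.2%, against about 80% stated. With r = 0.5 it is 90.8%, against 91% stated. Both reproduce.

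**Arm sizes.** 195 patients are 13 full blocks of 15, which gives 52/52/39/52. If TAU closes after N₀ patients, TAU stays at 4N₀/15 and the remaining 720 − N₀ are assumed to go 4:4:3 to the CRT arms. At N₀ = 195, TAU has 52, group and independent have 52 + 525 × 4/11 = 242.9 each, and intensive has 39 + 525 × 3/11 = 182.2.

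| TAU closed after | TAU | Group, independent (each) | Intensive | Power, group or independent v TAU: unadjusted / r = 0.5 | Power, intensive v TAU: unadjusted / r = 0.5 |
|---|---|---|---|---|---|
| never | 192 | 192 | 144 | 84% / 92% | 78% / 88% |
| 195 | 52 | 242.9 | 182.2 | 50% / 62% | 48% / 60% |
| 240 | 64 | 238.5 | 178.9 | 57% / 69% | 54% / 66% |
| 285 | 76 | 234.2 | 175.6 | 62% / 75% | 59% / 71% |
| 330 | 88 | 229.8 | 172.4 | 67% / 79% | 63% / 75% |
| 375 | 100 | 225.5 | 169.1 | 70% / 82% | 66% / 78% |

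The closing point is assumed. The 195 row would require recruitment to pause. At an even rate, 720 / (3 × 52) = 4.6 patients a week, so the 15-week follow-up alone adds about 69 and closure would come at 264 or later.

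The table counts CRT patients randomised after closure, of whom there would be 345 to 525 without a concurrent control.

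**Contrast.** If intensive CRT closed after 195 and the rest were split equally, each remaining arm would reach 52 + 525/3 = 227. Power would rise to 89% unadjusted and 96% with r = 0.5.

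**The case against.** **The committee needs an analyst.** Governance and monitoring calls the committee the only body with access, and somebody must prepare its reports. This is fair. On that reading the conflict with Governance and monitoring softens, but the conflict with Allocation and blinding remains, because its exception list omits the health economist. The strict reading would also catch any substitute analyst who is not a member, so the fix has to amend that section too.

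**The final economic analysis is largely fixed.** The Analysis section already sets perspectives, bootstrapped regression and the cost variations, and no one is named as final analyst. This limits the room for influence but does not remove the contradiction.

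**TAU closure was probably not intended.** The text also speaks of a treatment arm and of a therapy, which may mean CRT arms only, and an independent committee decides. This stands: the wording permits TAU closure without planning it.

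Some stronger readings are not supported:

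- *That outcome assessors would be unblinded.* Nothing sends interim results to assessors, and Allocation and blinding and Main challenges both protect them.
- *That TAU is the arm most likely to be closed, because CRT is taken to be effective.* The decision weighs cost as well as goal attainment, and TAU carries no CRT cost. A probability based on goal attainment alone does not measure the risk of closure.
- *That closing TAU would remove the comparator.* The contrasts would be weaker and partly non-concurrent, not impossible.
- *That the misprinted list, "iii) higher costs and better outcomes, or (iv) higher costs and better outcomes than a comparator", prevents a dominated arm from being identified.* The Analysis section lists all four quadrants, the interim plots every pair of comparators, and the missing probability is one minus the other three. It is a clerical slip.
- *That the committee may act only on ethical or safety grounds.* Governance and monitoring also has it advise on trial conduct. What remains is the difference between deciding and recommending.

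**Conclusion.** The point holds and the text is wrong as written. The health economist's interim task contradicts the list of unblinded staff and, on its plain reading, the statement on access to comparative data. The risk is to the analysis team.

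The closure wording does not exempt TAU. If TAU were closed after 195 to 375 patients, power of the primary contrasts at 0.3 SD would fall from about 78–84% to 48–70% unadjusted, or from 88–92% to 60–82% with r = 0.5.

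These figures assume a two-sided 5% level, full blocks of 15, a total held at 720, no loss to follow-up and 4:4:3 allocation after closure. Reduced blocks, which the protocol allows, take patients from the independent and TAU arms, so TAU would be smaller than shown. The committee's charter or the full protocol may settle some of this, but the article's own statements would still need to be reconciled.

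**What to change.** 1. In Interim analysis, state that only a CRT arm can be closed and that TAU is kept to the end of recruitment.
2. Have an already unblinded analyst, such as the randomisation statistician, run the interim from a pre-written script and report only to the data monitoring committee. The health economist can write the script, and stays blind until the final scripts are signed.
3. Name that analyst both in Allocation and blinding and in Governance and monitoring. Changing only one section would leave a contradiction in the other.
4. Reconcile Interim analysis with Governance and monitoring on whether the committee decides on closure or recommends it to the steering committee.
5. As a clerical correction, change the fourth quadrant in Interim analysis to higher costs with worse outcomes.

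The cost is wording in the protocol and the charter, plus the interim analyst's time. The documents do not say what capacity the randomisation statistician has, so this should be confirmed. The sample size need not change.

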### Governance and monitoring

The trial is sponsored by King’s College London, overseen by a National Institute for Health Research (NIHR) appointed ECLIPSE program steering committee, to which the trial’s independent data monitoring committee report. All members of the data monitoring committee are independent of the trial (are not involved with the trial in any other way and do not have competing interests that could impact the trial). The membership of all the committees can be found in Additional file 2: Table S2. The data monitoring committee is the only body involved in the trial that has access to the unblinded comparative data. It will receive and review the progress and accruing data of the trial and provide advice on the conduct of the trial to the trial steering committee. The role of its members is to monitor these data and make recommendations to the program steering committee on whether there are any ethical or safety reasons why the trial should not continue. Further details can be found in the data monitoring committee charter, which is based on DAMOCLES study group guidance [65]. Adverse events are reviewed by local principle investigators and stored locally. Serious adverse events are reported (emailed) within one working day to the local principle investigator and trial co-ordinator using password-protected forms. All serious adverse events are reviewed by a chief investigator to make a decision on whether or not they are definitely, possibly, or not related to the study intervention and whether they are expected or unexpected. All serious adverse events are anonymised and sent to a designated member of the data monitoring committee for their decision on whether they must be reported to the research ethical committee.

## Discussion

### Service user involvement

Service user involvement is an integral part of this study. Service users not only contributed to the study design but have also helped us develop the information sheets and consent forms and the publicity for the study, as well as advising us on how to approach potential participants. A service user and carer are also part of our steering committee. However, we have also chosen to meet our service user advisory group separately so that we can explain in more detail the issues we face and what our potential solutions might be. They can then provide advice that is not under time pressure or in the context of a large body of academics who may speak in jargon. This method of involvement has been suggested as important to ensure that service users feel they can provide worthwhile feedback [66]. Regular meetings are held to describe the recruitment, challenges and successes and the group is asked to advise on specific issues. The decisions of the user advisory group are then implemented and the minutes are available at meetings of the steering committee. Following advice on the effectiveness of user involvement [67, 68], we will ensure that our user advisory group provides value to our whole research programme by interviewing a sample of investigators each year to uncover and resolve any problems between the user group and the team. We will also ask the service user advisors to provide anonymous feedback on whether they think there are issues that have not been resolved satisfactorily or advice they feel that we ignored.

### Main challenges

The challenges fall into three areas: a changing context in the NHS; the availability of resources within teams; and block randomisation. Early intervention services have changed since the study was designed, as they now have specified waiting times and follow new NICE guidance on therapy packages. Both changes have affected how referrals are managed within teams. To overcome the new pressures, we will work closely with the clinical teams, team managers and care coordinators to ensure that the trial is not adding to these pressures. First, a full-time cognitive remediation therapist will be included in the early intervention team to provide early intervention staff an opportunity to refer their clients to CRT who might be on a waiting list for other therapy. Second, researchers will assist early intervention staff with risk-assessment reports (e.g. symptom assessments) and share a brief report on participant cognitive measures with the clinical teams, which will help them in their care programme approach for each individual, irrespective of whether they are involved in active therapy. Detailed cognitive assessments are usually not available in early intervention services, so this will be a benefit of choosing to take part in the trial.

Resources are always a difficulty, e.g. there may be a lack of suitable therapy rooms for CRT in some services, and we aim to help teams locate finance to re-use some unfurnished rooms. As CRT is not in NICE guidance, there is also a lack of experienced senior therapists who can provide specific supervision to more junior staff within a trust. We have responded by employing a senior clinical psychologist to offer this additional support across the sites and ensure continuity over the trial.

We developed our original block randomisation so that we could use the therapy resources as efficiently as possible and so blocks were defined as 15 participants. However, we potentially waste therapy resources with slow participant acquisition. Hence, we changed the blocks so that in some circumstances we can reduce the number of individuals who can be randomised. As with all trials there is a need to ensure blind assessment so we have also trained additional staff from each of the sites to provide extra support with some research procedures that might break the blind, e.g. inspecting clinical notes, and we will provide alternative raters in the case of any unblinding.

### Participant engagement and dissemination

Relevant research information will be available on the website, which is currently being developed (especially designed with participants in mind), as well as other social media (i.e. Twitter). This website will host presentations and peer-reviewed journal articles as they are produced to ensure accessibility. We will share our findings with our participants and participating teams through this method and also by sending newsletters at regular intervals to update them on the progress of the projects. Following advice from our user advisory group, participants will receive Christmas cards along with other promotional materials.

### Providing advice to the NHS

We are mindful that advice on implementation needs to come from different perspectives. Our three implementation models vary by therapist input and we will therefore have some detail on the effects on our key outcome variable, which is defined from the participants’ perspective – their goals as measured by the Goal Attainment Scale. But this is not all we will be measuring. We have the perspective of the service user participants on satisfaction with therapy and the method of provision, including therapy drop-out and the number of sessions received. We are collecting staff views so that we know what they consider appropriate levels of commitment and resource, as well as the organisational facilitators and barriers. We will include a provider perspective through the costs and cost-effectiveness of the different methods of providing therapy. All these perspectives will allow us to provide a balanced view of the different intervention methods so as to optimise their effects.

As well as a comprehensive overall plan for the best implementation method, our data will also allow us to discover whether therapy might need to be tailored to different individuals to provide the best effect. We will therefore investigate whether individual characteristics can predict larger or smaller benefits and, importantly, whether therapy might have a negative effect in some people. We will also investigate whether organisational factors, such as staff resources and background treatments, might affect successful CRT implementation.

All this information will allow: (i) policy makers to plan for this treatment; (ii) individual teams to understand what is required before and during implementation; and (iii) service users to receive the best individualised care to improve their recovery potential. Another of our work packages involves producing and evaluating an online training resource for this form of cognitive remediation. Together with the information on tailoring, this trial will allow smooth roll-out of the therapy into NHS services. Finally, the ECLIPSE programme will provide an implementation guide using the best available data.

## Trial status

Research protocol, version 1.3, 1 March 2017.

Recruitment start date, 1 June 2017; predicted recruitment end date, 1 January 2020.

## Abbreviations

ANCOVA: Analysis of covariance
CIRCuiTS: Computerised Interactive Remediation of Cognition – Training for Schizophrenia
CRT: Cognitive remediation therapy
ECLIPSE: Building Resilience and Recovery through Enhancing Cognition and Quality of Life in the Early Psychoses
NHS: National Health Service
NICE: National Institute for Health and Care Excellence
NIHR: National Institute for Health Research
